### Data and biosample collection

Study data will be collected by trained research staff. All blood samples will be taken from the right or left cubital fossa, after an 8–12 h fast, between 08:00–10:00 am. Dietary advice will be provided by appropriately trained dieticians. Personal information will be maintained separately from data, and is accessible only by study co-ordinators and principal investigators.

#### 1.1 Maternal anthropometry

Body weight will be measured (to the nearest 0.1 kg) using calibrated digital scales. Waist and hip circumferences will be measured (to the nearest 0.1 cm) using a standard tape measure according to the WHO guidelines (at the end of a normal expiration, at the midpoint between the lower margin of the last palpable rib and the top of the iliac crest, and around the widest portion of the buttocks, as the average of two measurements). Skin fold thickness measurement will occur according to the protocol published by Kannieappan and will involve triceps, biceps, subscapular skinfold thickness measurements plus arm circumference [59]. Measurements will be taken fortnightly during the weight loss phase (weeks 0–12), at week 16 and then 3 monthly for 12 months or until conception occurs. Post-conception measurements will occur at 12 and 26 weeks’ gestation and within 72 h of delivery.

#### 1.2 Maternal blood pressure

Blood pressure will be measured from the left arm, with an automated sphygmomanometer after participants have been seated for 5 min. All measurements will be taken with a large cuff.

#### 1.3 Fetal anthropometry

Weight will be measured (within 24 h of delivery) on digital calibrated scales. Length will be measured using a measuring board, and head circumference measured using a tape measure. Harpenden calipers will be used to measure skinfold thickness. in the mid-axillary line, triceps fold and subscapular fold. All measurements will be taken on the left side and repeated until a consistent, stable reading is obtained. Neonatal body fat estimation will be performed using the formula derived by Catalano [60]. There is no significant difference between this anthropometric estimate of body fat and total body electric conductivity.

#### 1.4 Laboratory assays

At each visit requiring a blood sample, 3 serum tubes, 1 lithium heparin tube and 1 fluoride EDTA tube with be taken. Samples will be mixed by inversion and centrifuged at 4 degrees Celsius. Plasma from the three serum tubes will be aliquoted into 5 microtubes for insulin/c-peptide, CRP/lipids and leptin with two spare samples. Plasma from the lithium heparin tube will aliquoted into 2 microtubes for free fatty acids. Plasma from the fluoride ETDA with be aliquoted into two microtubes for glucose. Plasma samples will be batched for analysis to minimise inter-assay error. Sample will be stored at − 80 degrees Celsius before analysis. Spare tubes will only be used in the event of a processing error. Our laboratory (Austin Pathology, Melbourne, Australia) has experience in measuring glucose, insulin, lipids, C-peptide, C-reactive protein (CRP), free fatty acids and leptin. The study database allows management of the samples. All analysis will be carried out on anonymised samples (Fig. 2).

**Fig. 2 Fig2:**
[figure not shown]
Example of template of recommended content for the schedule of enrolment, interventions, and assessments. X denotes tasks which must be completed in all study participants. (X) denotes tasks that are recommended but are not required

### Study management and governance

This two-arm, parallel group, randomized control trial is led by investigators based at the University of Melbourne. This is an academic institution comprising investigators from Melbourne Health, Austin Health, Royal Women’s Hospital, and Mercy Health. All involved institutions are based in Melbourne, Australia. The principal investigators will be responsible for all decisions in regard to management and delivery of the study. Data collected will be re-identifiable (coded) so that it remains confidential but could be identifiable if critical results are noted. All study information is treated as confidential and is securely stored. Data monitoring, protocol modifications, and reporting of serious adverse events will occur according to the specification of research ethics committees. All principal investigators will have access to the interim dataset and any decision to terminate the trial will be made by consensus. Principal investigators will be responsible for communication of the final results study results via publication in peer-reviewed journals.

### Statistical analysis/Power calculation

Most studies investigating the impact of maternal weight on pregnancy outcome have used the incidence of LGA neonates as the primary outcome. If this study used the same outcome, > 2000 women would be required to have sufficient offspring to achieve adequate power. This is clearly not practical. The HAPO data demonstrated a strong and continuous association between maternal fasting glucose at 24–32 weeks and pregnancy outcomes, including LGA neonates. Therefore, change in maternal fasting glucose at 26–28 weeks’ gestation can be used as a proxy for the incidence of LGA neonates.

In our pilot study, Phase 1 of the study demonstrated substantial weight loss (SWL) resulted in a reduction in maternal fasting glucose of approximately 10% (actual 9.12%, SE = 1.83, *n* = 24) compared to the modest weight loss (MWL) group (1.24%, SE = 1.40, *n* = 14). This is similar to previous studies by Sumithran [50] and Purcell [34]. In phase 3 of the pilot study (*n* = 10, MWL 3, SWL 7), glucose reductions were maintained at both 12 weeks’ gestation and 26–28 weeks’ gestation in both groups. Allowing for at least a moderate effect size of 0.6 for difference in percentage decrease in glucose at 26–28 weeks’ gestation (i.e. difference in means = 6, SD = 10; or slightly larger difference in means and larger SD) we require 45 women in each group to achieve 80% power.

We anticipate 45% of participants will not achieve a live birth within the study time-frame. This would include 20% drop-out during the weight loss phase. The anticipated drop-out rate is based on pilot data, on previous studies conducted by Purcell [34] and Rothberg [61], and by the lifestyle interventional study conducted by Mutsaerts [17]. We anticipate a further 25% of participants will fail to become pregnant within 12 months or will experience an early pregnancy loss at < 20 weeks’ gestation. This is based on the data from Kort et al. who found women with a mean BMI of 36 kg/m^2^ had a conception rate of 88% or 54% when losing ≥ 10% weight or < 10% weight, respectively [28]. We therefore require approximately 164 individuals.

The primary outcome will only consider those women who conceive and have a 75 g Oral Glucose Tolerance Test at 26–28 weeks’ gestation. Where appropriate, secondary outcomes will be analyzed both considering only those women conceive and also by intention to treat.

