### Randomization

Women will be randomized to the two treatment arms (Group A and Group B) using randomly permuted blocks of size 2, 4 or 6 (also randomly chosen) within 6 strata accounting for BMI (30–34.9; and 35–50 kg/m^2^), age (18–29 and 30–38 year-old), and parity (0 or 1+).

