#### Phase 1: Weight loss (Weeks 0–12)

##### Weeks 0 & 12 (all participants)

On arrival to the clinic, a fasting blood sample (20 ml) will be taken for measurement of plasma glucose, insulin, lipid profile (total cholesterol, LDL, HDL, triglycerides, non-esterified fatty acids (NEFA)), leptin and C-reactive protein (CRP)). The specified period of fasting is 8–12 h with blood samples drawn between 08:00 and 10:00 am. A urine and serum pregnancy test will be performed. Urinalysis will be performed for urinary ketones. Maternal anthropometry (weight, waist and hip circumference, skin fold thickness measurement) and blood pressure will be measured (see Data and Biosample collection 1.1 and 1.2).

Participants will be asked to avoid pregnancy using a medically proven form of contraception. Adequate methods of contraception include barrier contraceptives, hormonal contraceptives (oral, implanted, injectable) or mechanical products (intra-uterine device). The patient’s understanding of this will be documented. Standard pre-pregnancy medical advice for obese women planning pregnancy will be discussed. This includes the use of a multi-vitamin containing iodine 150μg (one tablet PO daily) and high dose folate (5 mg PO daily) [53].

The medical doctor will discuss the national guidelines for exercise with the participant using the NHMRC brochure titled “Australia’s Physical Activity and Sedentary Behaviour Guidelines for Adults”. Participants will be provided with a pedometer (Yamax 200S) and will be asked to wear the pedometer for 7 consecutive days (Week 2 of the weight loss phase). An average step count will be recorded. Exercise does not play a significant role in short-term weight loss but we wish to demonstrate that differences in weight loss between the groups are not due to exercise [54, 55].

Participants will be provided with a survey to take home and complete before the next study visit. This survey is based on the previously published Health in Pre-conception, Pregnancy and Post-birth (HIPPP) Study [56]. It is intended to assess areas including depression, anxiety, body image and activity level, which may impact health during pregnancy. This is expected to take around 1 h to complete. The decision to participate or not participate in this aspect of the study will not impact involvement in other aspects of the study.

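### The primary comparison is sized as an unadjusted difference in percentage decrease, while the stated outcome is the 26–28 week glucose level; ANCOVA on week-0 glucose would settle the conflict and add power at no real cost

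*Protocol article*

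**What the plan says.** All references are to the Protocol article.

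- **Sizing metric** (Statistical analysis/Power calculation): "Allowing for at least a moderate effect size of 0.6 for difference in percentage decrease in glucose at 26–28 weeks’ gestation". The planning values are "difference in means = 6, SD = 10", and the result is "we require 45 women in each group to achieve 80% power". No covariate or correlation enters the calculation.
- **Outcome definition** (Abstract; Outcome measures): the primary outcome is the fasting plasma glucose from the oral glucose tolerance test (OGTT) at 26–28 weeks, which is a level. The primary aim speaks of a reduction of at least 10% compared with the modest-weight-loss arm.
- **Baseline value** (Weeks 0 & 12, all participants): "a fasting blood sample (20 ml) will be taken for measurement of plasma glucose, insulin, lipid profile".
- **Stratification** (Randomization): the strata are built "accounting for BMI (30–34.9; and 35–50 kg/m^2^), age (18–29 and 30–38 year-old), and parity (0 or 1" or more).
- **Analysis set** (Statistical analysis/Power calculation): "The primary outcome will only consider those women who conceive and have a 75 g Oral Glucose Tolerance Test at 26–28 weeks’ gestation". The Outcome measures section also leaves out women with a positive early OGTT.

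The article names no primary model. It neither says that the analysis will be unadjusted nor rules out covariates.

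**The concern.** The article gives two different variables for one primary comparison. A level at 26–28 weeks and a percentage decrease from week 0 have different variances and respond in opposite directions to a chance difference in baseline. The only comparison described numerically is the percentage decrease, as a plain difference between two means.

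Dividing by baseline is not the same as adjusting for it. A percentage-change score in effect fixes the slope on baseline at 1. With equal variances at the two times, the real slope is the correlation ρ, which is below 1. The arm with the higher week-0 glucose therefore shows a larger decrease without any treatment effect.

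This matters more here than in a trial that analyses everyone randomised. The primary set is restricted by conception and by having the OGTT, so randomisation does not guarantee balance in week-0 glucose, BMI, age or parity among the women compared. At stake are some power, some protection against baseline imbalance, and a choice between two documented metrics that could otherwise be made after the data are seen.

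**Working it through.** **1. The plan's own figure.** Inputs from the power calculation: difference 6, SD 10, so d = 0.6, with 45 per group. Alpha is not stated; two-sided 0.05 is assumed because it reproduces the plan (one-sided 0.05 needs only 35 to 36 per group).

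- Required n per group: 44 by the normal approximation and 44.6 by the t-test, so 45.
- Power at 45 per group: 80.4% (t-test).
- Total: 90/(1 − 0.45) = 163.6, so 164.

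The sizing reproduces as an unadjusted two-sample comparison.

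**2. Power with baseline adjustment.** Let ρ be the correlation between week-0 and 26–28 week glucose, with equal variance σ² at both times. The article gives no ρ, so a range of 0.3 to 0.8 is assumed.

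- Variance of a change score: 2σ²(1 − ρ).
- Residual variance under ANCOVA: σ²(1 − ρ²).
- Ratio: (1 + ρ)/2, so the effective d is 0.6/√((1 + ρ)/2).

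The closed-form column uses the noncentral t with four covariate degrees of freedom removed. It credits no explanatory gain to BMI, age or parity. The simulation (4,000 trials, assumed mean 4.9 mmol/L, 6% effect, SD of percentage change about 10) compares percentage change without and with week-0 glucose as a covariate.

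| ρ (assumed) | Ratio | Closed-form adjusted power | Gain over 80.4% | Simulated: unadjusted → adjusted | Simulated gain |
|---|---|---|---|---|---|
| 0.3 | 0.65 | 93.7% | 13.3 | 81.0% → 93.5% | 12.5 |
| 0.5 | 0.75 | 90.1% | 9.7 | 81.2% → 88.8% | 7.6 |
| 0.7 | 0.85 | 86.2% | 5.8 | 80.3% → 85.0% | 4.7 |
| 0.8 | 0.90 | 84.3% | 3.9 | 80.1% → 82.7% | 2.6 |

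The gain is therefore roughly 3 to 13 points, and smallest when ρ is high.

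**3. Effect of a baseline difference.** Suppose week-0 glucose among the women analysed is 2% higher in the substantial-weight-loss arm (about 0.1 mmol/L on a mean near 5). This is an assumption, not a figure from the article.

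- Percentage decrease: the contrast moves by (1 − ρ) × 2 points in favour of that arm. At ρ = 0.5 this is 1.0 point, so a true 6 reads as about 7.
- Unadjusted level: the contrast moves by ρ × 2 points against that arm. At ρ = 0.5 this is also 1.0 point, so a true 6 reads as about 5.
- ANCOVA: the shift is removed.

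The simulation with an imbalance of 0.2 SD (0.2 × 0.49 = 0.098 mmol/L, or 2% of 4.9) at ρ = 0.5 agrees for percentage change. The unadjusted estimate is 7.0 or 5.1, depending on the direction of the imbalance; the adjusted estimate is 6.0 to 6.1. With no true effect, the unadjusted test rejects in 7.1% to 7.4% of trials and the adjusted test in 5.0%.

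**The case against.** The strongest reply is that a sizing assumption is not an analysis. The article states no primary model, and covariates are commonly left to a statistical analysis plan, which is not shown. Sizing without adjustment is conservative: it reaches the stated 80%, and later adjustment can only be expected to help. This stands. A reader might infer that the trial is losing about 10 points of power, or that baseline imbalance will go uncorrected. The article supports neither: the first rests on one assumed correlation (ρ near 0.5, and only in the closed form), the second on an analysis that is nowhere stated.

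It can also be said that the planners had room to spare. The pilot standard errors imply SDs of 1.83 × √24 = 9.0 and 1.40 × √14 = 5.2, pooled about 7.8. The pilot difference of 9.12 − 1.24 = 7.88 is then a standardised effect near 1.0. That is fair, but it is a weight-loss-phase result and not a pregnancy result.

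Finally, the main threat in this analysis set is selection after randomisation. The article itself cites conception rates of 88% and 54% according to weight loss achieved. Adjusting for measured baseline variables lessens that problem but does not restore the randomised comparison. This also stands.

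What the reply does not answer is that the article describes the primary comparison in two incompatible ways, and that the one it uses for sizing handles baseline poorly.

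**Conclusion.** The point holds as an inconsistency of metric together with an improvement that is nearly free. It is not an error in the sample size: 45 per group, 80% power and 164 in total are arithmetically right.

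If the analysis follows the sizing metric, it would forgo roughly 3 to 13 points of power for ρ from 0.8 down to 0.3. It would also be open to a shift of about 1 of the planned 6 points for a 2% baseline difference at ρ = 0.5. Both sizes are conditional: the correlation, the equal variances and the imbalance are assumed, because the article gives none of them.

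**What to change.** State the primary analysis as a linear model (ANCOVA) of 26–28 week fasting glucose on arm, with week-0 fasting glucose and the stratification factors (BMI, age, parity) as covariates. Report the adjusted mean difference with its 95% confidence interval. If a percentage effect is wanted, as the primary aim suggests, use log glucose at both times and report the ratio of adjusted geometric means. Keep percentage decrease as a descriptive summary.

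This removes the choice between level and change: with baseline in the model, the level and the absolute change give the same treatment estimate. The sample size can stay as it is.

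The cost is a change of wording and about four degrees of freedom (one for baseline, three for the two-level factors). It needs no new data, visits or participants. The text should say that adjustment does not remove the selection from analysing only women who conceive and have the OGTT.

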All standard pregnancy care, including the decision to proceed with an early 75 g Oral Glucose Tolerance Test (OGTT), will occur at the discretion of the treating maternity team. If gestational diabetes is diagnosed at any gestation, treatment should proceed per usual local guidelines. The diagnosis of gestational diabetes will be documented in the participant file and all medical therapy used to manage gestational diabetes will be recorded. Given that these women will not have an OGTT at 26–28 weeks’ gestation, glucose samples from these participants cannot be used in the analysis of the primary outcome. Study samples should otherwise be collected per the study protocol (Fig. 1).

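### 164 women yield about 35, not 45, in the modest-weight-loss arm on the plan's cited conception rates, and leave no margin for pregnancy loss or the early-OGTT exclusion, so 80% power is not secured

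*Protocol article*

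**What the plan says.** All the sizing is in the protocol article, under Statistical analysis/Power calculation. The effect is set by "Allowing for at least a moderate effect size of 0.6 for difference in percentage decrease in glucose", spelled out as "difference in means = 6, SD = 10; or slightly larger difference in means and larger SD", and the conclusion is that "we require 45 women in each group to achieve 80% power".

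The loss is then built up in two parts that total 45% of participants: 20% drop-out in the weight-loss phase, and a second part described as "We anticipate a further 25% of participants will fail to become pregnant within 12 months or will experience an early pregnancy loss". The second part is said to rest on a study of women with a mean BMI of 36 who "had a conception rate of 88% or 54% when losing ≥ 10% weight or < 10% weight, respectively". The section ends: "We therefore require approximately 164 individuals".

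Three other places bear on this:

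- The Group A and Group B sections expect weight loss of at most 3% and of 10–15%. The two arms therefore fall on opposite sides of the 10% cut in the cited rates.
- The Phase 3b section says of women diagnosed with gestational diabetes early that "glucose samples from these participants cannot be used in the analysis of the primary outcome". Outcome measures repeats the exclusion for women with a positive early OGTT.
- The power section itself limits the primary outcome to women who conceive and have the OGTT at 26–28 weeks.

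**The concern.** One loss figure is applied to both arms, although the source given for it shows conception differing by 34 points (88% against 54%) along the very contrast that is randomised. A shorter time to conception is itself a secondary aim, so the investigators expect the arms to differ in this respect.

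Two further losses come between conception and the primary endpoint: pregnancy loss before 20 weeks, and exclusion after a positive early OGTT. The first is named but appears to have almost no room within the 25%. The second does not appear in the 45% at all.

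If the plan overstates the evaluable numbers, a null result on fasting glucose would be read against 80% power that the trial may not have had.

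**Working it through.** **Inputs.** From the power section: effect 0.6 (difference 6, SD 10), 45 per group, drop-out 20%, further loss 25%, conception 88% and 54%, total 164. Allocation is taken as 1:1, from the equal group sizes and the "randomly permuted blocks of size 2, 4 or 6" in the Randomization section, so 82 per arm. The significance level is not stated; two-sided 5% is assumed because it reproduces the 45 (one-sided 5% would give 35). Power is for an unadjusted two-sample t-test.

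**1. The plan's own figures reproduce.** The t-test needs 44.6 per arm, i.e. 45, and 45 against 45 gives 80.4%. The inflation is 90 / 0.55 = 163.6, i.e. 164.

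**2. Expected conceptions by arm.** Assume the 20% drop-out applies equally: 82 × 0.80 = 65.6 completers per arm.

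- SWL: 65.6 × 0.88 = 57.7
- MWL: 65.6 × 0.54 = 35.4
- Total: 93.2 (unrounded)

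With no drop-out at all in MWL the figure is 82 × 0.54 = 44.3, still below 45.

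**3. Power at those numbers.** 57.7 against 35.4 at 0.6 gives 79.4% (80.3% by the normal approximation, which gives 81.2% for 45 against 45). The imbalance costs about 1 point.

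**4. What the 25% has to cover.** The simple average of the cited rates is (88 + 54) / 2 = 71%. Non-conception among completers is 29%, which is 0.80 × 29% = 23.2% of those randomised. That leaves 25 − 23.2 = 1.8 points for early pregnancy loss. As a share of conceptions this is 1.8 / (0.80 × 71) = 1.8 / 56.8 = 3.2%.

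**5. Adding the losses that have little or no allowance.** The protocol gives no rate for either, so these are assumed values. Both are applied equally to the two arms, multiplying each arm by (1 − pregnancy loss) × (1 − early-OGTT exclusion).

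| Pregnancy loss | Early-OGTT exclusion | SWL | MWL | Power at 0.6 |
|---|---|---|---|---|
| 0% | 0% | 57.7 | 35.4 | 79.4% |
| 5% | 5% | 52.1 | 32.0 | 75.2% |
| 10% | 0% | 52.0 | 31.9 | 75.0% |
| 10% | 10% | 46.8 | 28.7 | 70.4% |
| 15% | 10% | 44.2 | 27.1 | 67.9% |
| 20% | 15% | 39.3 | 24.1 | 62.6% |

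No combination in the range 0–20% and 0–15% reaches 80%.

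**The case against.** **The shortfall in MWL does not by itself break the power.** A reader might infer that 35 women instead of 45 means the stated 80% is missed. The documents do not support that step. The same rates put about 58 women in the other arm, and 93 in total is more than the 90 planned. One point of power is within rounding for a total given only as approximate. This objection stands.

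**Nor is 35 a ceiling.** The 20% drop-out is given only overall; if MWL lost nobody, 44 would remain. The cited rates are for women grouped by the weight loss they achieved, not for randomised arms, and the 71% gives the two groups equal weight. The 25% is described as based on those data, not as equal to them, so the 3.2% left for pregnancy loss is a reconstruction. These cautions stand. They qualify the exact figures but do not create a margin. For example, if only 50–80% of SWL women lose 10% or more and the rest conceive at 54%, power before any further loss is 76–78%, lower than above.

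**The material shortfall rests on assumed rates.** This is correct, and it is why the result can only be a range.

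**The effect size may be conservative.** The pilot's weight-loss phase gives a difference of 9.12 − 1.24 = 7.88. Its standard errors imply SDs of 1.83 × √24 = 9.0 and 1.40 × √14 = 5.2, a pooled SD of 7.8, and an effect of about 1.0. At 44 against 27, power would be 81% at 0.7 and 98% at 1.0. This limits the practical consequence, but those are pre-pregnancy glucose data; only 10 pilot women (3 MWL, 7 SWL) contributed to the pregnancy phase. It does not restore 80% at 0.6, which is what the plan claims.

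**Conclusion.** The point holds in a limited form. The arithmetic from 45 per group to 164 is correct, but its inputs do not deliver 45 evaluable women in each group. On the cited conception rates, with equal 20% drop-out, about 58 SWL and 35 MWL women conceive, which still gives about 79% power. The 80% is nevertheless not secured. The 25% leaves about 1.8 points for early pregnancy loss, and the 45% has no term for the early-OGTT exclusion that the protocol itself imposes. Any realistic value for either takes power below the stated level: 75% with 10% pregnancy loss, 70% with a further 10% exclusion, and 79% down to 63% over the ranges shown.

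These figures assume a two-sided 5% unadjusted t-test, equal drop-out, equal further losses in both arms, and each arm conceiving at its cited rate. The direction is well supported; the size beyond the first point depends on rates that the protocol does not give.

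**What to change.** In Statistical analysis/Power calculation:

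1. Replace the single requirement of 45 in each group with expected evaluable numbers by arm, starting from about 58 SWL and 35 MWL conceptions, and state the drop-out assumed in each arm.
2. Add two explicit allowances, for pregnancy loss before 20 weeks and for exclusion after a positive early OGTT. Give the source or pilot basis for each rate.
3. Restate the power at 0.6 for those unequal numbers as a range over plausible rates, with the significance level and sidedness.

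The cost is a rewritten paragraph and a less favourable power statement. Trial status has recruitment ending in February 2018, and the change asks for no further recruitment. It leaves the primary analysis population and the analysis method as they are.
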